#### **9.2.2 Serious adverse events (SAEs)**

A serious adverse event is any untoward medical occurrence or effect that results in death; is life threatening (at the time of the event); requires hospitalisation or prolongation of existing inpatients' hospitalisation; results in persistent or significant disability or incapacity; is a congenital anomaly or birth defect; or any other important medical event that did not result in any of the outcomes listed above due to medical or surgical intervention but could have been based upon appropriate judgement by the investigator.

An elective hospital admission will not be considered as a serious adverse event. The investigator will report all SAEs to the sponsor without undue delay after obtaining knowledge of the events.

The sponsor will report the SAEs through the web portal *ToetsingOnline* to the accredited METC that approved the protocol, within 7 days of first knowledge for SAEs that result in death or are life threatening followed by a period of maximum of 8 days to complete the initial preliminary report. All other SAEs will be reported within a period of maximum 15 days after the sponsor has first knowledge of the serious adverse events.

### **9.2.3 Suspected unexpected serious adverse reactions (SUSARs)**

**9.2.4** Not applicable.

### **9.3 Annual safety report**

**9.4** Not applicable.

### **9.5 Follow-up of adverse events**

All AEs will be followed until they have abated, or until a stable situation has been reached. Depending on the event, follow-up may require additional tests or medical procedures as indicated, and/or referral to the general physician or a medical specialist.

SAEs need to be reported till end of study within the Netherlands, as defined in the protocol

### **9.6 Data Safety Monitoring Board (DSMB) / Safety Committee**

Based on the nature of this study, a Data Safety Monitoring Board (DSMB) is considered unnecessary. According to the NFU Risk Classification and Monitoring, the risk of this study is negligible. Therefore, there is no need to perform interim analyses concerning safety and effectiveness of the treatment during the course of this trial. An independent monitor will be involved in this study.

## 10. STATISTICAL ANALYSIS

Data analyses will be based on intention-to-treat analyses and will be performed using R software. Descriptive statistics will be described in frequency tables or presented as means and standard deviations.

### 10.1 Primary study parameter(s)

The primary outcome of the study is prolonged grief symptoms as measured by the TGI-SR+. To test the hypothesis that prolonged grief symptoms will decline during the treatment of comorbid insomnia we will use two analytic strategies. First, we will use visual inspection. The data of each participant will be plotted separately. We will then inspect changes in the mean level between the baseline phase and the treatment phase. The mean level refers to the mean of all the data points in each phase. Differences in the mean are the first indication of a treatment effect. Next, we will inspect the slope or trend in each phase. An upward trend in symptom severity during the baseline phase vs. a downward trend during the treatment phase would be the strongest indicator of a treatment effect. Finally, we will look at the latency of change. In general, effects occurring closer to the start of the treatment phase would be a strong indicator of a direct treatment effect. Effects occurring more distal to the start of the treatment phase could potentially be due to other factors and would be considered weaker evidence for a treatment effect (Kazdin, 2019). In the current study, we expect a delayed treatment effect since the most effective parts of the CBT-I sleep restriction and stimulus control are introduced in the second session. Therefore, the latency of change will be looked at exploratively.

Second, we will use Tau-U to quantitatively assess the differences between the baseline and intervention phase at an individual level. Tau-U is a non-overlap index (between the phases) that corrects for possible trends in the data (Parker et al., 2011). Hereafter, a randomization test will be used to assess the overall effect of the intervention. The randomization test is based on the random assignment of baseline length (i.e., moment of phase change; (Michiels & Onghena, 2019). This non-parametric test compares the mean difference of all possible baselines (10 per person in the current study) with the mean difference between the actual baseline and treatment phase. The place in the rank order of the mean differences determines the p-value of the test. The null hypothesis is that there is no difference between the baseline and treatment phases. The alternative hypothesis is that there is a difference between the two phases. To check for the potential effects of receiving treatment through telehealth versus face-to-face treatment, we will also run the randomization tests for the two treatment options separately.

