Following recruitment, participants will be randomly assigned based on a computer-generated list to different lengths of baselines (or wait time), ranging between five and 14 weeks (see Table 1 for an overview). During this phase, participants will be asked to complete weekly short online questionnaires assessing insomnia symptoms (Insomnia Severity Index, ISI: (Morin, 1993; Dutch version: Bastien et al., 2001)) and PGD symptoms (TGI-SR+: Lenferink et al., 2022) experienced during the past week. The weekly assessment of insomnia and PGD symptoms will continue during the treatment phase. The treatment phase consists of 6-7 weekly therapy sessions and at four-week post-treatment a booster session, and continued weekly monitoring of insomnia and PGD symptoms. The continued monitoring allows for the capturing of delayed treatment effects. In order to (visually) inspect long term effects, insomnia and PGD symptoms will be assessed again three-months post-treatment. A weblink to online questionnaires will be sent via e-mail to participants, CBT-I will be delivered by a psychologist in training to become a healthcare psychologist, supervised by a registered healthcare psychologist, specialised in insomnia. CBT-I consists

of 6-7 weekly individual, face-to-face sessions of 1-2 hours according to the Dutch CBT-I protocol (Verbeek & van de Laar, 2023). Depending on the location of the participant, these sessions can be held either at the Heymans Institute or online using a video conference program. At four weeks post-treatment, a booster session will be planned to evaluate sleep health and, if necessary, repeat certain treatment components.

CBT-I components are:

Psycho-education: providing information about the function and regulation of normal sleep and the consequences of disturbed sleep.

Sleep hygiene: giving information on healthy lifestyle that can improve sleep and on behaviors that disrupt sleep.

Stimulus control: strengthening the association between bed (and bedroom) and sleep by only going to bed when sleepy and leaving the bed when awake for longer than 30 min and getting up at a fixed time.

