#### 4.4 Sample size calculation

Based on a prior small pilot study on CBT-I effects on prolonged grief symptoms (Sveen et al., 2021) and studies on CBT-I effects on depression symptoms (e.g., Christensen et al., 2016; van der Zweerde et al., 2020), we estimate a large effect size (*Cohen's d* = 1.0) on prolonged grief and insomnia symptoms. An a priori power analysis was conducted using the single case designs shiny web-app for power calculations (Bouwmeester & Jongerling, 2020). Based on power of .80, a total of 26 measurements per participant, of which minimally five during baseline phase, followed by minimally 12 measurements during the treatment (and continued monitoring) phase and an alpha of .05, sample size of 19 is required (see Table 1 for an overview). A total of 20 patients will be enrolled to ensure sufficient power. CBT-I provided generally elicits a low dropout rate (e.g., Lancee et al., 2016), in case a participant drops out, they will be replaced by another participant.

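### Separate randomization tests for telehealth and face-to-face do not test whether the effect differs between delivery modes, which is their stated purpose

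*Protocol*

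**What the plan says.** Section 10.1 of the protocol gives the purpose of the check: "To check for the potential effects of receiving treatment through telehealth versus face-to-face treatment". The only analysis named for it is that "we will also run the randomization tests for the two treatment options separately". The hypotheses of the randomization test are set out in the same section: "The null hypothesis is that there is no difference between the baseline and treatment phases", and "The alternative hypothesis is that there is a difference between the two phases". They concern the two phases, not the two modes.

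Section 10.2 makes the ISI analysis identical to that of the TGI-SR+, so the check is repeated for insomnia.

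On how mode is decided, section 3 says: "Depending on the location of the participant, these sessions can be held either at the Heymans Institute or online using a video conference program". Sections 5.1 and 8.3 say the same. Section 8.2 randomises only the length of the waiting period. No expected or minimum number per mode is given.

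Section 4.4 sets the sample size (19 required, 20 enrolled, power 0.80, alpha 0.05, d = 1.0, 26 measurements) for all participants together.

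**The concern.** A question about a difference between two groups needs a statistic that contrasts them. Here each group gets its own test against zero change, and no contrast, interaction statistic or interval for the difference is named. Two p-values of this kind mislead in both directions:

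- One significant and one non-significant result is no evidence that the modes differ. It arises easily when the effects are equal, because each subgroup test has less power than the test on all 20.
- Two significant results are no evidence that the modes are equal. Both effects can be non-zero and still differ.

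Because mode follows location, even a proper contrast would be observational. The protocol labels the latency-of-change inspection exploratory, but not this check. What is at stake is an ancillary statement about delivery mode, for both the TGI-SR+ and the ISI.

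**Working it through.** **Inputs from the protocol.** 26 weekly measurements; baseline of 5 to 14 weeks (10 possible lengths); alpha 0.05; d = 1.0; 80% power at N = 19; 20 enrolled. Section 10.1 expects a delayed effect, because the most effective components start in the second session.

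**Assumptions, not in the protocol.** Split by mode (10/10, 14/6, also 16/4); autocorrelation of weekly scores (AR 0 to 0.3, also higher); shape of the effect; d read as within-person SD units.

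**Test.** For participant i, D_i = baseline mean minus treatment mean. The statistic is the mean of D_i. Its reference distribution comes from redrawing each participant's baseline length from 5 to 14 weeks.

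**The plan's own figure.** An immediate 1 SD step gives simulated power of about 0.999 at N = 19 with independent errors and 0.97 with AR 0.5, not 0.80. Power of 0.80 at N = 19 appears with a one-week delay and AR 0.4 (0.801), or with a step of about 0.53 SD (0.803). The protocol does not give the autocorrelation, trend or SD definition entered in the web-app, so the figure is under-determined and not shown to be wrong.

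**Route 1: take 80% power at N = 19 as given.** Normal approximation, two-sided: power(n) = Φ[(1.960 + 0.842)·√(n/19) − 1.960].

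- n = 10: Φ(2.802 × 0.725 − 1.960) = 0.529
- n = 14: 0.672
- n = 6: 0.350

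With equal true effects, the chance of one significant and one non-significant result is p1(1 − p2) + p2(1 − p1).

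- 10/10: 2 × 0.529 × 0.471 = 0.498
- 14/6: 0.672 × 0.650 + 0.350 × 0.328 = 0.552

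Simulation calibrated to the same 80% gives 49-50% (10/10), 54-56% (14/6) and 59-60% (16/4).

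**Route 2: take a full 1 SD effect in both modes and vary its shape.** The figures are the simulated share of trials with one significant and one non-significant test. Ranges reflect repeated runs.

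| Effect shape | Errors | 10/10 | 14/6 |
|---|---|---|---|
| One-week delay or four-week build-up | AR 0.3 | 48-50% | 53-55% |
| Immediate step | AR 0.3 | 21-25% | 32-33% |
| Immediate step | independent | 9-10% | 19-22% |

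A one-week delay with independent errors gives about 44% at 10/10. Over AR 0 to 0.3 and these two splits, the delayed or gradual shapes give about 44-55% and the immediate step about 9-34%.

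Outside that grid:

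- Immediate step, AR 0.5: 32% (10/10) and 38% (14/6).
- Immediate step, independent errors, 16/4 split: 37%.
- Two-week delay, AR 0.3: 41-45% over the three splits.
- No effect in either mode: 9-10%.

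**Direct comparison.** A permutation test of mode labels on the D_i rejects in 4-6% of trials when the effects are equal, for every split and scenario tried. That is the error rate a test of the stated question should have.

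**The case against.** The strongest defence is that the sentence promises only a check. The protocol gives no rule for reading the two p-values. A reader might infer that the trial will probably report that CBT-I works in one mode and not the other, or that mode does not matter. The document says neither, so that inference is a guess about future reporting. The check could also be meant to show that the overall effect is not carried by one mode, and within-mode results bear on that, though weakly. This stands as a limit on what can be claimed. It does not rescue the method, because the stated purpose is a comparison of the modes and no comparison is planned.

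Delivery mode appears in no objective or endpoint and does not enter the sample size. That stands too, and it lowers the severity.

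A reader might also take discordant results to be frequent under any conditions. They are not: with an immediate step, independent errors and an even split the figure is about 9%. The higher figures need a delayed or gradual effect, autocorrelation or an uneven split. The protocol supports the first of these and is silent on the other two.

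Finally, individual plots and Tau-U values are already planned and could be shown by mode. The protocol does not commit to that display, so this softens the gap without closing it.

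**Conclusion.** Wrong as written, low severity. That two within-mode tests of zero phase difference do not test a difference between modes follows from the hypotheses in section 10.1 and needs no simulation. It applies to the TGI-SR+ and, through section 10.2, to the ISI.

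The size of the problem is conditional. With identical 1 SD effects, AR 0 to 0.3 and a 10/10 or 14/6 split, discordant results occur in about 44-55% of trials under a one-week delay or four-week build-up, and in about 9-34% under an immediate step. The delayed case is closer to what the protocol expects. The split, autocorrelation and exact effect shape are assumptions.

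The documents do not support the further inference that the primary conclusion or the sample size is affected.

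**What to change.** In section 10.1, replace the two separate tests with one direct comparison. Take each participant's phase difference (baseline mean minus treatment mean) and compare it between modes, for example as the difference in means with a 95% confidence interval, or with a label-permutation test. Report the estimate and interval for each mode beside it. Label the comparison exploratory and non-randomised, since mode follows location. Section 10.2 then carries it over to the ISI.

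The cost is about one sentence. No regression model is needed, and data collection, the primary randomization test and the sample size stay as they are. The downside is a wide interval at N = 20, which reflects how little the trial can say about delivery mode.

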### **10.2 Secondary study parameter(s)**

The secondary study outcome are insomnia symptoms as measured by the ISI. The analysis of the insomnia symptoms will be identical to the analysis of prolonged grief symptoms described above.

### **10.3 Other study parameters**

Sociodemographic and loss-related characteristics (age, gender, education level, kinship to the deceased, gender of the deceased, cause of death, expectedness of the loss) clinical characteristics at baseline will be used to describe the sample.

### **10.4 Interim analysis (if applicable)**

Not applicable

## **11. ETHICAL CONSIDERATIONS**

### **11.1 Regulation statement**

This study will be conducted according to the principles of the Declaration of Helsinki (2013) and in accordance with the Medical Research Involving Human Subjects Act (WMO). Moreover, the General Data Protection Regulation (GDPR in Dutch: Uitvoeringswet Algemene Verordening Gegevensbescherming)

### **11.2 Recruitment and consent**

Recruitment of bereaved adults ( $\geq 18$  years) who lost a first-degree relative or partner will take place via localized Google AdWords advertisements and websites for organizations for bereaved persons, linking to a research website ([www.onderzoekrouw.nl](http://www.onderzoekrouw.nl)). Additionally, people who have participated in an earlier longitudinal survey and indicated an interest in future studies will be asked to visit the website. On the website, interested bereaved adults can access information about the study (see E1) and can provide informed consent on a secure online survey program, Qualtrics. After providing online informed consent (see E2), they can complete a screener for sociodemographic and loss-related characteristics, sleep disorders (HSDQ; Kerkhof et al., 2013) and PGD (TGI-SR+; Lenferink et al., 2022).

People who meet the established cut-off values for insomnia disorder and PGD based on screener results, will be invited to meet online (via a secure online meeting program) or to visit the Heymans Institute of the University of Groningen for a clinical interview to assess PGD (Traumatic Grief Inventory-Clinician Administered, TGI-CA; Lenferink et al., 2023) and insomnia disorder (Structured Clinical Interview for DSM-5 Sleep Disorders, SCISD; Taylor et al., 2018).

Prior to the clinical interviews, participants will be provided with the study information letter once more (see E1) and an informed consent form (E2) to provide written informed consent. When participants meet all inclusion criteria and none of the exclusion criteria, they can start the waiting period. Before the start of the clinical interview, participants will have the opportunity to ask any questions or concerns they may have to the researcher that is present. In addition, the information letter (E1) notes that participants may ask any questions they may have by email.

### **11.3 Objection by minors or incapacitated subjects (if applicable)**

Not applicable.

### **11.4 Benefits and risks assessment, group relatedness**

A benefit of the current study is that it investigates a promising new approach to the treatment of prolonged grief disorder. Current evidence-based treatments for prolonged grief disorder have shown limited success rates, with no more than 50% of clients reporting clinically relevant improvement (for reviews: Doering & Eisma, 2016; Johannsen et al., 2019). Recent studies have suggested that insomnia symptoms might be causally implicated in the persistence of severe, disabling grief reactions (e.g., de Lang et al., 2023, 2024; Lancel et al., 2020). Insomnia therapy has shown promising effects in other stress and mood-related disorders such as depression (Gee et al., 2019) and post-traumatic stress disorder (Ho et al.,

2016) and a small pilot study has shown promising effects of insomnia therapy on prolonged grief symptoms in bereaved parents (Sveen et al., 2021). Therefore, it is likely that targeting insomnia symptoms in people with both prolonged grief disorder and insomnia disorder will reduce both insomnia and prolonged grief symptoms.

A benefit for participants in the study is that we will use CBT-I, the gold standard treatment for insomnia worldwide, which has been investigated in numerous studies, and is recommended in clinical practice (see: Riemann et al., 2023). While CBT-I has minimal risks, some components carry specific concerns. Stimulus control therapy, which involves leaving the bedroom if unable to sleep and using the bed solely for sleep and sex, may increase the risk of falls for elderly or mobility-impaired participants. To prevent this, such participants will not be instructed to leave the bed. Sleep restriction therapy, another CBT-I component, requires limiting time in bed to the average duration of sleep. Although effective, this approach can cause short-term side effects like reduced reaction times and performance impairments, common among those with insomnia. To enhance safety, participants will spend at least five hours in bed each night and will be advised to avoid driving or operating heavy machinery if they feel excessively sleepy during the therapy's early stages. Over time, these side effects typically diminish as the therapy takes effect.

Additionally, the study involves repeated measurement of prolonged grief and insomnia symptoms, which could evoke negative emotions. However, prior research indicates that bereaved participants often find value in contributing to scientific knowledge. To minimize distress, only validated, concise questionnaires with completion times under five minutes will be used. Overall, the study offers the potential for significant improvements in both insomnia and prolonged grief symptoms, with minimal risks.

### **11.5 Compensation for injury**

The researchers asked for dispensation for compulsory insurance in medical research in human subjects, because they do not expect additional risks for the participants (article 7 paragraph 5 WMO). We refer to our discussion in the previous section on benefits and risks. However, the liability of the researcher or provider is assured. The sponsor/investigator has a liability insurance which is in accordance with article 7 of the WMO.

### **11.6 Incentives (if applicable)**

In addition to receiving evidence-based treatment for insomnia disorder, participants will receive 5 euros for each set of completed questionnaires (26 in total) with an extra 50 euro bonus for completion of the follow-up questionnaires.

## **12. ADMINISTRATIVE ASPECTS, MONITORING AND PUBLICATION**

### **12.1 Handling and storage of data and documents**

The researchers will manage data and documents confidentially. Paper documents resulting from this study, such as consent forms, are stored separately in a secured location at the RUG. Contact data will be stored in a digital file for the purpose of administering the assessments at the planned moments. In a key file, each participant is assigned a personal code, which links research data to individual participants. These codes are not based on the initials, birth-date or other participant related characteristics. The code list will start at 101 in ascending order. The coordinating investigator and principal investigator the only persons with access to the key file. In addition, the code list will be stored on Qualtrics our secure online questionnaire partner. This is needed in order to send the questionnaires with participant number to the correct participant. The research data will be processed and analysed in separate files that contain no direct links to the participants. Digital and paper data necessary to reproduce analysis and quality checks will be kept for 15 years at RUG conform local and official regulations (GDPR) as stated in the RUG data storage protocol

### **12.2 Monitoring and Quality Assurance**

The coordinating investigator, principal investigator, and research assistants are the only persons with access to the key file. The research data will be processed and analysed in separate files that contain no direct links to the participants. Digital and paper data necessary to reproduce analysis and quality checks will be kept for 15 years at RUG conform local and official regulations (GDPR) as stated in the RUG data storage protocol

